## Abstract

**Background:**

The Chronic Disease Co-Care (CDCC) Pilot Scheme is a government-subsidized program that aims to provide targeted copayment for the screening and management of hypertension, diabetes mellitus and pre-diabetes in the private healthcare sector. Studies have found that concurrent screening and management with a multi-disciplinary intervention is cost-saving because of the reduction in the rates of premature mortality, complications and utilization of public health services. This study aims to evaluate the quality of care, acceptability, effectiveness and cost-effectiveness of the CDCC Pilot Scheme.

**Methods:**

Quality of care will be evaluated by the standards achieved by the program in each criterion in the domains of structure, process and outcomes of care. Site visits and two serial questionnaire surveys at 6 and 12 months will be conducted for the structure of care. Operational data, including the provision of diagnosis and treatment, as well as participants’ health status will be extracted to evaluate the process and outcomes of care. Participants’ acceptability will be evaluated on experience (accessibility, facility, continuity of care and communication), satisfaction (perceived usefulness, continuation and recommendation) and enablement in 548 CDCC participants at 3 and 12 months by telephone surveys. Evaluation of the effectiveness and cost-effectiveness is a 1-year comparative cohort study using longitudinal data on changes in disease control parameters between CDCC and non-CDCC participants at baseline and 12 months. Costing questionnaires on the set-up and operation costs of the Scheme among service providers, and direct medical costs incurred from public and private service utilization among participants within 12 months from enrolment will be assessed. The incremental costs incurred for an additional participant in the CDCC Pilot Scheme to achieve target disease control outcomes after 12 months will be reported as an indicator for cost-effectiveness.

**Discussion:**

The quality of care and effectiveness of the CDCC Pilot Scheme in enhancing the health outcomes of the Scheme participants will be examined. Standards of good practice and recommendations for quality enhancement will be established to inform service planning in similar cross-sector screening and management programme.

**Trial registration:**

NCT06310148; 2024-03-22.

**Supplementary Information:**

The online version contains supplementary material available at 10.1186/s12875-025-02765-6.

## Background

The Hong Kong public healthcare system is faced with ever-increasing challenges brought about by an aging population, greater prevalence of chronic diseases, rising costs of medical care, as well as increased citizen expectations from health systems. Reconfiguration of the primary healthcare (PHC) system to a preventive-oriented system equipped with multi-disciplinary teams could enable healthcare systems to be more effective and efficient. There is compelling international evidence suggesting that having a family doctor (FD) as a regular source of primary care is associated with significantly lower odds of avoidable hospitalization in chronic disease patients [1–3], as well as improved patient outcomes [4, 5].

To alleviate the growing burden placed by chronic diseases on the public healthcare system, the Hong Kong government has developed the Primary Healthcare Blueprint outlining strategies to strengthen district-based primary care services across Hong Kong. Among these strategies include the early identification and intervention of chronic diseases through disease screening at the community level, streamlining the referral system, and engaging the private healthcare sector to improve accessibility to quality PHC.

Specifically, the Chronic Disease Co-Care (CDCC) Pilot Scheme was launched in November 2023 to provide targeted subsidy for the screening and management of hypertension (HT), diabetes mellitus (DM) and pre-diabetes (pre-DM) in the private healthcare sector. Studies have found that screening adults for DM and pre-DM is cost-saving from a health system’s perspective and can lower pre-mature mortality rates [6, 7]. In addition, concurrent screening and management of HT and DM with a multi-disciplinary intervention has been shown to be cost-saving in part because of the reduction in complications and subsequent utilization of public secondary and tertiary health services [8, 9].

Participants of the CDCC Pilot Scheme will receive protocol-driven multi-disciplinary risk assessment and management in private PHC allowing for timely intervention to prevent complications of HT/DM. To ensure the quality of the provision of continuous and holistic primary care, Scheme FDs must be registered in the Primary Care Directory and use the PHC reference frameworks as the standard care protocol for PHC services. District Health Centres (DHC) and DHC Express throughout the territory will serve as case managers to support FDs and coordinate with healthcare service providers to deliver network allied health services, laboratory service and drug service. According to the diagnosis, FDs will recommend comprehensive health management plans, provide necessary medication treatment, and set health targets together with participants. To support participants in disease prevention and management, nurse-led clinic will provide education, health assessment, and counselling services; whereas allied health professionals (including optometrists, podiatrists, dietitians, and physiotherapists) will provide individualised intervention services for participants. Each Scheme participant will be entitled to co-payment for services received under the CDCC Pilot Scheme which include subsidised FD, allied health, drug, and laboratory investigation services.

In order to assure that the CDCC Pilot Scheme is delivered with the intended care and achieves the expected health benefits, we will evaluate its quality of care, acceptability, effectiveness and cost-effectiveness to inform future PHC planning and policy.

## Aims and objectives

This study aims to evaluate the quality of care, acceptability, effectiveness and cost-effectiveness of the CDCC Pilot Scheme. The objectives of this study are to:

Measure the adherence to the standards of care criteria by healthcare providers participating in the Scheme;Evaluate participant acceptability by self-reported outcomes on enablement, experience and satisfaction level about the services of the Scheme;Evaluate the effectiveness of the Scheme in improving health outcomes among CDCC participants over 12 months; and.Determine the provider costs and cost-effectiveness for delivering the CDCC Pilot Scheme relative to its effectiveness on participants health outcomes.

We hypothesize that:

Healthcare providers participating in the Scheme would achieve over 70% adherence for the standards of care criteria;60% of participants will report an increase in patient enablement levels after 12 months;90% of participants will report patient satisfaction 12 months after enrolment;A greater proportion of participants in the CDCC Pilot Scheme would achieve targets for disease control outcomes after 12 months compared to the comparison group; and.The Scheme would be cost-effective based on an incremental cost-effectiveness ratio (ICER) lower than the willingness-to-pay threshold of 1 annual gross domestic product (GDP) per person.

## Methods

### Study design

This study consists of three parts. First, the evaluation of the quality of care is a cross-sectional study including site visits at DHC/DHC Express, administration of two serial quality of care questionnaires at 6 and 12 months among service providers, and extraction of the Scheme operational data from the eHealth database and DHC IT module, which are electronic databases used by the DHC/DHC Express to record participant data. Second, the evaluation of participant acceptability is a longitudinal cohort study by telephone surveys among CDCC participants at 3 and 12 months after CDCC enrolment. Third, the evaluation of the effectiveness and cost-effectiveness is a 1-year comparative cohort study using longitudinal data on health outcomes and healthcare utilization (and hence direct medical costs) among CDCC and non-CDCC participants at baseline and 12 months. Costing questionnaires on the set-up and operation costs of the Scheme will be distributed among service providers.

### Subjects

To evaluate the quality of care, all operators of the DHC/DHC Express, and selected FDs and allied health professionals, will be asked to complete quality of care questionnaires. All participants who have enrolled into the CDCC Pilot Scheme between 1 Jan and 30 Jun 2024 will be included in the evaluation of the standards on process and outcome of care.

A convenient sample of 548 CDCC participants would be recruited from all 18 DHC/DHC Express between 1 Apr 2024 and 31 Aug 2024 to complete a survey on self-reported outcomes on participant acceptability and enablement. A conservative target of 140 participants for each diagnosis (i.e., normal, pre-DM, HT and DM) will be set to ensure different patients are equally represented.

The effectiveness and cost-effectiveness of the Scheme will be evaluated by comparing the differences in health outcomes and healthcare utilization rates among CDCC and non-CDCC participants at 12 months after enrolment. Records for CDCC participants enrolled between 1 Jan and 30 Apr 2024 who meet the inclusion criteria to participate in the CDCC Pilot Scheme will be included as the intervention group, while participants in the comparison group would be non-CDCC participants recruited in the community through collaboration with local networks and organizations. Participants ≥ 45 years, without a known diagnosis of HT and/or DM, and provide informed consent are eligible to join the study.

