### Sample size calculation

The sample size needed for evaluating participant acceptability is based on the proportion of participants who showed an increase in enablement, measured by the Patient Enablement Instrument (PEI), one year after enrolment into the CDCC Pilot Scheme. Previous studies showed that 55.6–72.2% of participants reported PEI score > 0 after entering structured programmes for DM and/or HT [10–12]. Assuming the proportion of CDCC participants with PEI score > 0 at 12 months to be 50%, 383 CDCC participants are required with 5% margin of error and significance level of 5%. To allow for about 30% attrition, the sample size required will be 548.

The sample size for evaluating the effectiveness and cost-effectiveness was determined based on the difference in the proportion of patients achieving the targeted outcome for disease control after 12 months between CDCC participants and the comparison group. Previous studies evaluating the 12-month effectiveness of the multi-disciplinary Risk Assessment and Management Program for DM or HT implemented in public primary care in Hong Kong found that the proportion of participants achieving treatment target (glycated hemoglobin [HbA1c] < 7.0% or systolic/diastolic blood pressure [BP] < 140/90mmHg) increased by 5.40% [13] or 1.18% [14], respectively after 12 months, compared to patients receiving usual care. Assuming a conservative 3% increase in the proportion of participants achieving treatment target after 12 months in the CDCC group, a total of 378 participants with pre-DM, HT and/or DM are required to detect difference at a power of 80% with a significance level of 5%/ According to the Hong Kong Population Health Survey 2020, the prevalence of undiagnosed HT and DM among individuals aged 45–84 was 15.4% and 4.6%, respectively [15]. Previous studies reported that the prevalence of pre-DM was 2.3–8.9% in Hong Kong [15, 16]. Taking a prevalence of approximately 20% in total for pre-DM, HT and/or DM, and accounting for an attrition of 30%, a total of 1,886 non CDCC participants will be required.

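### Equal diagnosis targets in the acceptability survey do not match the overall 60% and 90% hypotheses or the 5-point margin

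*Protocol article*

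**What the plan says.** **Sampling (Protocol article, Subjects).** "A convenient sample of 548 CDCC participants would be recruited from all 18 DHC/DHC Express", with this target inside it: "A conservative target of 140 participants for each diagnosis (i.e., normal, pre-DM, HT and DM) will be set to ensure different patients are equally represented".

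**Hypotheses (Aims and objectives).** Both are for participants as a whole, not by diagnosis: "60% of participants will report an increase in patient enablement levels after 12 months" and "90% of participants will report patient satisfaction 12 months after enrolment".

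**Precision (Sample size calculation).** One proportion is used: "Assuming the proportion of CDCC participants with PEI score > 0 at 12 months to be 50" per cent, from which "383 CDCC participants are required with 5% margin of error and significance level of 5" per cent. Then: "To allow for about 30% attrition, the sample size required will be 548". The background rates are from diagnosed patients: "55.6–72.2% of participants reported PEI score > 0 after entering structured programmes for DM and/or HT". No diagnosis shares, weights or design effect appear.

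**Analysis (Data analysis).** Enablement, experience and satisfaction are to be summarised by descriptive statistics. Neither weighting nor estimates by diagnosis are mentioned. PEI is listed as a primary outcome; satisfaction is secondary.

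**The concern.** If the four targets are met, each diagnosis contributes a quarter of the sample whatever its share of the Scheme. A simple pooled percentage then estimates the average over an equal mix, whereas the hypotheses and the sample size are worded for CDCC participants overall. The two coincide if enablement does not vary by diagnosis, or if the Scheme's own mix is close to equal. The article offers no evidence for either. Variation is plausible, since care follows the diagnosis and the later survey asks about treatment and management, which normal participants may hardly receive.

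At stake is the meaning of the overall figures set against 60% and 90%, and the precision claimed for the first of them. If the results are left unweighted, they describe a mix set by the recruitment targets. If they are weighted to the Scheme, the 5-point margin no longer applies.

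**Working it through.** **1. The plan's own figure.** For one proportion from a simple random sample, n = 1.96² × p(1 − p) / d². With p = 0.5 and d = 0.05, n = 3.8416 × 0.25 / 0.0025 = 384.2. The stated 383 agrees within rounding. 383 / 0.70 = 547.1, so 548 recruits. The figures reproduce, as a simple random sample of one population.

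**2. Precision by diagnosis.** 140 × 0.70 = 98 completers each. At p = 0.5 the margin is 1.96 × √(0.25 / 98) = 9.9 points.

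**3. Pooled figure against Scheme value.** Let W be the share of Scheme enrolees who are normal, p_N their PEI > 0 rate, and p_D a common rate in the three diagnosed groups.

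- Pooled with equal targets: 0.25 p_N + 0.75 p_D
- Scheme value: W p_N + (1 − W) p_D
- Difference: (W − 0.25)(p_D − p_N)

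The article gives neither W nor p_N. Assumptions: p_D = 64% (about the middle of the cited 55.6–72.2%), p_N = 30–50%, W = 40–80%.

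| p_N | W | Pooled | Scheme value | Difference (points) |
|---|---|---|---|---|
| 50% | 40% | 60.5% | 58.4% | 2.1 |
| 50% | 80% | 60.5% | 52.8% | 7.7 |
| 30% | 40% | 55.5% | 50.4% | 5.1 |
| 30% | 80% | 55.5% | 36.8% | 18.7 |
| 64% | any | 64% | 64% | 0 |

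The difference would change sign if normal participants had the higher rate.

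**4. Margin after weighting.** With equal numbers per diagnosis and p(1 − p) = 0.25 in each, weighting to Scheme shares W_h has design effect 4 × ΣW_h². The margin is 1.96 × √(0.25 × design effect / 383). Example for 40/25/25/10: 4 × (0.16 + 0.0625 + 0.0625 + 0.01) = 1.18, and 1.96 × √(0.25 × 1.18 / 383) = 5.4 points.

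| Mix, normal/pre-DM/HT/DM (%) | Basis | Design effect | Effective n | Margin (points) |
|---|---|---|---|---|
| 25/25/25/25 | equal mix | 1.00 | 383 | 5.0 |
| 40/25/25/10 | assumed | 1.18 | 325 | 5.4 |
| 60/15/18/7 | assumed | 1.68 | 228 | 6.5 |
| 71.1/8.9/15.4/4.6 | article's prevalences, upper pre-DM figure | 2.16 | 178 | 7.4 |
| 80/0/15.4/4.6 | article's 20% total | 2.66 | 144 | 8.2 |

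The last two rows use population prevalences that the article cites to size the non-CDCC group. They are only a proxy for people who chose to enrol, and they treat the categories as exclusive.

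**The case against.** The strongest reply is that the article never says the four groups will be pooled without weights. Tables by diagnosis and a weighted overall percentage are both descriptive statistics, and a full analysis plan may specify them. That stands: the unweighted figure is one reading of the plan, not a statement in it. It does not rescue the sample size, however, which is fixed in this article. A weighted figure for the Scheme will not have a 5-point margin unless the real mix is near equal.

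It also stands that equal targets are a legitimate way to secure estimates for small groups, that they are targets and may not be filled exactly, and that HT and DM can overlap. Drawing the background PEI rates from diagnosed patients does no harm to the calculation itself, because 50% is the value with the largest variance.

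Some stronger readings are tempting, but the documents do not support them:

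- **That the pooled result will be too high, or will reverse the conclusion.** The direction follows from assuming a lower rate in normal participants. In the cases above where the Scheme value misses 60% and the pooled figure does not, the pooled figure is 60.5%, only half a point clear. The article states a hypothesis but no decision rule.
- **That the satisfaction result loses a stated precision.** No margin is given for the 90% hypothesis. Only the mismatch of population applies there.
- **That four targets of 140 contradict 548.** 548 / 4 = 137, so 140 is a rounding up that covers the requirement.

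**Conclusion.** The concern holds in limited form. Recruitment is by equal diagnosis targets, while the hypotheses and the PEI margin are for CDCC participants overall, and nothing in the article connects the two. A pooled, unweighted proportion would answer a question about an equal mix.

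How far that lies from the Scheme value is unknown. It is about 2–19 points under the assumed rates and shares, and zero if the diagnoses share one rate. The firmer result is on precision: for an overall figure weighted to the Scheme, the margin is about 5.4–8.2 points over the mixes shown, not 5. That range rests on 383 completers split equally, p = 0.5 in each group, exclusive categories, and mixes that are assumed or borrowed from population prevalence.

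**What to change.** 1. Report PEI > 0 and satisfaction by diagnosis, stating the margin of about ±9.9 points for PEI with 98 completers per group at p = 0.5.
2. Define mutually exclusive diagnosis categories, with a rule for participants who have more than one diagnosis and for the missing diagnoses that the Discussion reports.
3. Judge the 60% and 90% hypotheses on an overall figure post-stratified to the actual diagnosis mix of Scheme enrolees, taken from eHealth and the DHC IT module. Name the enrolment window that defines the mix.
4. Restate the overall PEI margin with the design effect from that actual mix, in place of 5 points.
5. State that the interval is model-based, because selection probabilities are unknown in a convenience sample, and that weighting by diagnosis does not remove convenience-sampling bias.

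The cost is a weighting step on data already being extracted, and a wider stated margin. No new recruitment is needed if that margin is accepted. Keeping 5 points with equal targets would take about 452 to 1,021 completers (383 × 1.18 to 383 × 2.66), or 646 to 1,459 recruits after 30% attrition.

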### Data collection

#### Evaluation of the quality of care

The CDCC Pilot Scheme will be evaluated based on a systematic and user-centric approach described by Donabedian et al. [17], where components of the programme are classified into a taxonomy of structure, process and outcome of quality of care. Structure refers to the conditions which care is provided including infrastructure (facilities and equipment), human resources, staff training and organizational characteristics. Process refers to the set of activities that go on within and between healthcare providers and patients, i.e., the provision of diagnosis, treatment, prevention, and education etc. Outcomes refer to the changes in patients’ health that can be attributed to healthcare, and may include changes in health status, patient knowledge, behavior and patient satisfaction.

Evidence-based quality of care indicators and standards on the structure, processes and outcomes will be established based on the operation protocols developed by the Primary Healthcare Commission, and in consultation with the service providers. The evaluation framework is attached in Appendix A. Site visits at DHC/DHC Express by the research team were carried out between June and August 2024 to understand the programme operation. A site visit form with a standardized flow and questions asked during the site visit was developed to ensure consistency in data collection. Data on the structure of care are collected through questionnaires completed by the operation managers at DHC/DHC Express at 6 and 12 months, and by a representative sample of FDs and allied health professionals at 12 months. Data on the process and outcomes of care will be extracted from eHealth and DHC IT module. Compliance to standards of care across different service providers will be measured based on the evaluation framework.

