## Discussion

The CDCC Pilot Scheme is a territory-wide programme to advocate early screening and management of chronic diseases with private-public partnership in the community setting. The implementation of the Scheme involves various stakeholders including the Primary Healthcare Commission, DHC/DHC Express, FDs and allied health professionals. A timely evaluation of the Scheme at this pilot stage is needed to assure the cross-sector collaboration works as expected and to inform strategies for quality enhancement in the future. Guided by the three domains of quality of care (structure, process and outcome), key stakeholders were involved at the initial phase to develop the evaluation criteria and standards, incorporating feedback from service providers based on real-world practice. The inclusion of various stakeholders and providers, and adoption of both subjective (self-reported outcomes) and objective (site visits and health parameters) data collection methods enhance the validity and reliability of the results. Results of the evaluation could shed light on good practices that has already been adopted and inform future guidelines to improve service quality.

Previous evaluation studies on the Risk Assessment and Management Program in Hong Kong, a chronic disease management programme implemented in public primary care, discussed approaches to facilitate the evaluation of multi-disciplinary programme [26]. They include coordinating stakeholder collaboration and communication, continuous feedback and planning meetings, stakeholder endorsement and validation, development of evaluation framework and operation definitions, and ensuring data quality. These recommendations have been incorporated in the current evaluation.

The CDCC Pilot Scheme was officially launched in the November 2023. To date, the evaluation framework has been developed, and have already conducted all site visits to DHC/DHC Express. The recruitment of participants for the participant experience and enablement survey and control group non-participants are in progress. We anticipate the major challenges in the evaluation to be:

Stakeholder endorsement and validation.

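### The CDCC effectiveness cohort is closed at 30 April 2024 while comparator recruitment has no stated window and runs later, so the 12-month threshold and cost comparisons may be partly confounded with calendar time

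*Protocol article*

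**What the plan says.** Methods, Subjects, defines the intervention group for effectiveness and cost-effectiveness as "Records for CDCC participants enrolled between 1 Jan and 30 Apr 2024 who meet the inclusion criteria". The comparison group is "non-CDCC participants recruited in the community through collaboration with local networks and organizations", with no start or end date. The same section does date the other participant cohorts. For the process and outcome standards it says "All participants who have enrolled into the CDCC Pilot Scheme between 1 Jan and 30 Jun 2024 will be included", and the acceptability survey recruits from 1 April to 31 August 2024.

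Two other statements place comparator recruitment in time. Under Evaluation of the quality of care: "Site visits at DHC/DHC Express by the research team were carried out between June and August 2024". In the Discussion, the authors "have already conducted all site visits to DHC/DHC Express", and in the same account, "The recruitment of participants for the participant experience and enablement survey and control group non-participants are in progress".

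Both groups are followed for 12 months from their own enrolment. Under Outcome measures, the disease-control target is an absolute level for hypertension (BP below 140/90 mmHg) and for diabetes (HbA1c below 7%), and a reduction in HbA1c for pre-diabetes. Data analysis compares attainment by chi-squared test and by logistic regression with unnamed confounders, and uses the difference in attainment as the ICER denominator.

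**The concern.** Twelve months of follow-up keeps the time of year constant within a person. It does not keep it constant between groups that entered in different months. If one group is measured against a fixed threshold in January to April and part of the other in late summer or after, anything that moves BP or HbA1c with the calendar enters the group difference. Entry is exposed too: participants have no known diagnosis and disease is found by screening, so the month of screening can affect who counts as hypertensive.

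At stake are the primary difference in target attainment, the ICER that divides by it, and the 12-month utilisation and cost comparison, whose follow-up periods cover different calendar time. Which months each group covers is settled when the cohorts are selected. If one group has no records from some months, a regression model cannot supply them.

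**Working it through.** **Dates side by side**

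| Group | Enrolment | 12-month point |
|---|---|---|
| CDCC, effectiveness | 1 Jan to 30 Apr 2024 (Subjects) | Jan to Apr 2025 |
| Comparators, earliest | not stated | not stated |
| Comparators, latest | after completion of site visits that ran June to August 2024 (quality-of-care section; Discussion) | about August 2025 or later, if the visits ran into August |

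If the visits ran into August, the latest comparators enter at least three to four months after 30 April. How many do so is unknown.

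**Which outcomes are exposed**

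- Hypertension and diabetes targets: absolute level at 12 months, so exposed.
- Pre-diabetes target and secondary changes in mean BP or HbA1c: within-person over a nominal year, so largely protected. The protection is weaker for CDCC laboratory values, because the Discussion (data quality) uses the latest record and not one fixed at 12 months.
- Utilisation and direct medical costs: accumulated over different calendar periods, so exposed.

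**Size, for systolic BP only**

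There is no seasonal figure in the documents to reproduce. From the sample size section I use the 3-point planning effect and the prevalences: undiagnosed hypertension 15.4%, diabetes 4.6%, pre-diabetes 2.3 to 8.9%, about 20% in total. The rest is assumed: a between-group shift s of 1, 2 or 3 mmHg, SD 12 to 18 mmHg, attainment p of 50 to 80%, normal BP, and no calendar overlap. The direction of s is arbitrary.

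Step 1, outcome shifted only: change = Φ(Φ⁻¹(p) + s/SD) − p. For example, p = 0.5, SD = 12 and s = 3 gives Φ(0.25) − 0.5 = 9.9 points.

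Step 2, the same shift at screening and at 12 months. A hypertension case is SBP of 140 or more at entry, and attainment is SBP below 140 at 12 months, under a bivariate normal model. Assumed: population mean 120 to 130, SD 13 to 16, correlation 0.4 to 0.7, fall over the year 0 to 10 mmHg. With s = 3, attainment moves by 2.0 to 6.8 points, against 3.2 to 12.0 in the same model with only the outcome shifted. Selection at entry therefore offsets part of the effect.

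Step 3, dilute by the hypertension share of cases: 15.4/(15.4 + 4.6 + 8.9) = 53% to 15.4/20 = 77%. The low end of each range is multiplied by 0.53 and the high end by 0.77.

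| s (mmHg) | Step 1, HT cases | Step 1, all cases | Step 2, HT cases | Step 2, all cases |
|---|---|---|---|---|
| 1 | 1.5 to 3.3 | 0.8 to 2.6 | 0.6 to 2.2 | 0.3 to 1.7 |
| 2 | 3.0 to 6.6 | 1.6 to 5.1 | 1.3 to 4.5 | 0.7 to 3.5 |
| 3 | 4.3 to 9.9 | 2.3 to 7.6 | 2.0 to 6.8 | 1.1 to 5.2 |

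Step 4, overlap. If half of the comparators enrolled in the CDCC months, each figure halves; the last cell becomes about 0.5 to 2.6 points. With full overlap the effect is zero.

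**The case against.** No start date for comparator recruitment is given, so a large share may have enrolled in the same months as the CDCC cohort. The sentence that reports comparator recruitment in progress says the same of the acceptability survey, which was planned to close on 31 August 2024; if that held, the article was written around August and no entry in autumn is documented. A condensed article may leave the recruitment calendar and the covariate list to the full protocol, and the unnamed confounders could include month. No statement in the documents says that BP or HbA1c varies by season.

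Most of this stands and limits the point. What remains is that the CDCC window is fixed, comparator recruitment ran beyond it, and nothing aligns the two. A month term in the model works only where both groups have records in the same months, and the cohort definition does not secure that.

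Three stronger readings are tempting and are not supported:

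- **Baseline and 12-month values fall in different seasons for the same person.** They are nominally a year apart, so they do not.
- **The result is biased against the Scheme.** That needs a seasonal direction that the documents do not give.
- **The bias is far larger than the planning effect.** Large figures come from assuming bigger shifts and no overlap, counting hypertension cases only, and ignoring the offset from screening at entry.

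**Conclusion.** The concern holds in a limited form. Group is partly tied to calendar time. This affects the 12-month hypertension and diabetes thresholds, the ICER denominator to the extent that it rests on them, and the utilisation and cost comparison. The misalignment is certain for only part of the comparison group, and the direction of any bias is unknown.

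Under assumed systolic shifts of 1 to 3 mmHg, the effect on overall attainment could be of the same order as the planned 3 points. It falls in proportion to calendar overlap and to the hypertension share of cases. No size is offered for HbA1c or for costs, because the documents give nothing to base one on. This is a worthwhile and inexpensive improvement to cohort selection; it does not show that the comparison is invalid.

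**What to change.** 1. State the start and end dates of comparator recruitment.
2. Extend the planned CDCC extraction for the effectiveness cohort to cover the months in which comparators are recruited. Extraction to 30 June 2024 is already planned for the quality-of-care part, so this lengthens a date range.
3. Match or weight CDCC records to comparators by calendar month of baseline, and report the distribution of baseline and outcome months by group.
4. Include calendar month in the adjusted logistic model, where step 2 has secured overlap.

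**Cost.** No new recruitment is needed. The later CDCC 12-month records arrive some months later, but no later than the comparators' own 12-month data. CDCC records from months without comparators would carry little or no weight. Follow-up of later enrollees also extends further beyond the December 2023 to December 2024 operating-cost period, and the cost analysis should say so.
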